### 1.4. Originality and Innovation

Due to the relatively recent implementation and widespread use of electronic prescription modules, there are very few comparable studies available, and none with our specific approach in the Spanish population. Therefore, our project offers significant innovation relative to the existing body of evidence.

Additionally, the project will incorporate digital elements in both the assessment of risk factors and the telematic intervention we will offer, leveraging new technologies to benefit patients.

Finally, the psychoeducational intervention will include a component of the “peer support” approach, in which stabilized patients contribute their own testimonies to help improve adherence in others. Such interventions have been shown to be effective in individuals with schizophrenia (Orsi et al., 2021) and bipolar disorder (Kelly et al., 2019), and may help ensure that the intervention is not perceived as coercive. The goal is not to “scold” patients for nonadherence but to help them understand the long-term benefits of sustained treatment adherence. The intervention is designed to respect patient autonomy and the right to refuse treatment. The program focuses on health literacy and shared decision-making, empowering participants to align their therapeutic choices with their personal recovery goals.

The ADHERA intervention is grounded in the Health Belief Model (HBM) and Motivational Interviewing principles. The conceptual model posits that the intervention influences adherence through a specific pathway: first, by improving clinical insight (knowledge of the disorder); second, by shifting attitudes (reducing perceived barriers and increasing perceived benefits of treatment); and third, by enhancing behavioral regulation (developing routines and digital self-monitoring). This progression is designed to transform adherence from a reactive behavior driven by external clinical pressure into a proactive health-seeking behavior.

### 1.5. Study Objectives

The objectives of our project are as follows:To validate self-reported digital adherence questionnaires using dispensing data from the MUP on antipsychotic medication as the gold standard.To identify factors associated with poor adherence by exploring correlations between various sociodemographic variables—available through the Patient Portal—and medication exposure as measured via the MUP.To evaluate the effectiveness of the intervention by reassessing patient adherence six months after the intervention.

### 1.6. Working Hypotheses

Our working hypotheses are:Pre-post comparison: Treatment adherence will increase following the intervention.Risk factor association: Statistically significant risk factors associated with poor adherence will be identified.Validity: The PROMs (Patient-Reported Outcome Measures) used will demonstrate concurrent validity with the objective data provided by the MUP.Feasibility and acceptability: Both the intervention and the overall study will be well tolerated and positively received by participants.

## 2. Materials and Methods

### 2.1. Setting and Design

This project will be carried out in the Psychiatry Departments of four hospitals in the Community of Madrid associated with the Instituto de Investigación Sanitaria Fundación Jiménez Díaz: Hospital Universitario Fundación Jiménez Díaz, Hospital Rey Juan Carlos, Hospital General de Villalba, and Hospital Infanta Elena. This protocol combines three complementary methodological perspectives: (1) a validation study; (2) an observational study; and (3) a single-arm pre-post study to evaluate the intervention. All patients identified with poor adherence will receive the same psychoeducational program; the pre-intervention measurement will serve as a comparator.

Figure 1 shows the outline of the project.

This protocol describes a study with three design perspectives to achieve our objectives:Validation study to explore the accuracy of digital self-report questionnaires.Observational study for identifying factors associated with non-adherence.Pre-post study to assess the effectiveness of the intervention

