### 2.3. Sample Size Calculation

According to our preliminary data, there are 5458 patients in our hospitals diagnosed with schizophrenia or bipolar disorder and with active antipsychotic dispensing registered in the MUP. Of these, an estimated 90% are registered on the Patient Portal, yielding an initial estimated sample of 4900 people.

Considering that completion of self-administered questionnaires on the Patient Portal is estimated to be around 30%, we expect an approximate sample of 1640 patients to perform the validation calculations for the adherence scales.

The sample size was calculated using G*Power (v3.1) for a one-sample means test (alpha = 0.05, power = 95%, effect size d = 0.5), yielding a minimum of 52 participants. This was based on previous studies exploring the ability of educational interventions to improve medication adherence in the medium term (Loots et al., 2021). Accounting for an anticipated dropout rate of up to 50%, the adjusted minimum is 104. We therefore set a recruitment target of 110 participants, well within the estimated pool of 656 patients expected to present with poor adherence.

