### 2.4. Procedure and Intervention

Project is expected to start in September 2026. We will access the MUP database and cross-reference it with data from the Patient Portal to identify our target sample, that is, those patients who received antipsychotic dispensations who also appear as active users of the Patient Portal. Within the entire sample, we will identify factors associated with adherence issues in the six months prior to the study. The entire sample will then be invited via a message through the Patient Portal to complete the self-report adherence questionnaires.

Finally, the subset of the sample identified with adherence problems will be the target sample for the intervention. Adherence problems to antipsychotics in people with schizophrenia or bipolar disorder are around 40–50%, although the variability in the studies is considerably high (Lingam & Scott, 2002). From the identified pool of patients with poor adherence, a recruitment target of 110 participants has been established. This sample size was determined using G*Power (v3.1) for a one-sample means test (alpha = 0.05, power = 95%, effect size d = 0.5), which requires a minimum of 52 participants (Loots et al., 2021). The final target of 110 accounts for an anticipated dropout rate of up to 50%, ensuring sufficient statistical power despite the high attrition typically observed in this clinical population.

The intervention program will be designed by clinical psychologists with experience in treating patients with bipolar disorder and schizophrenia after a review of the best protocols available in the literature. Presumably, participants will receive psychoeducational materials on the importance of adherence and the potential for mishap management. Tablet handling tips and medication-taking schedules will be reviewed. Participants will also be invited to a telehealth intervention comprising 10 online group psychotherapy sessions delivered via videoconference. These sessions will include cognitive-behavioral measures to manage adherence problems, and adherence will be monitored. Psychotherapy sessions will be led by clinical psychologists, and two sessions will feature testimonials from stabilized patients (See Figure 2).

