### 2.8. Statistical Analysis

Statistical analyses will be performed using R software version 4.5.3 and SPSS software version 30.0, or the latest versions available. All tests will be two-tailed, with 95% confidence intervals, and the level of statistical significance will be set at a *p*-value less than 0.05. The Morisky and Haynes scales (Morisky et al., 1986) will be measured prior to the intervention and again at the end of the sessions, and changes will be analyzed using Pearson’s correlation and simple regression. On the other hand, we will compare the total duration of antipsychotic exposure in the 6 months prior to the intervention with that in the 6 months following the intervention. Similarly, we will compare the average doses to which the sample was exposed before and after the intervention by calculating the recommended daily doses received.

To validate self-report questionnaires, sensitivity, specificity, positive predictive value, and negative predictive value will be calculated using medication collection data from the MUP as the gold standard. ROC curves will be constructed to determine the empirically optimal cut-off for classifying adherence, using the Youden index and reported with 95% confidence intervals, with PRE2DUP-derived antipsychotic exposure as the reference standard.

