To explore factors associated with higher or lower adherence, a logistic regression will be conducted, with adherence as the dependent variable. Adherence will be operationalized using the PRE2DUP method (Tanskanen et al., 2015; Taipale et al., 2016), generating two continuous outcomes: total duration of antipsychotic exposure (days) and average daily dose in DDDs (Tanskanen et al., 2015). These continuous variables will be used as dependent variables in all regression analyses. Furthermore, linear correlations will be performed between adherence levels (using percentage of adherence as a continuous variable) and various potentially implicated factors. To identify factors independently associated with non-adherence, a multivariable logistic regression model will be constructed, incorporating sociodemographic and clinical variables as independent predictors and adjusting for potential confounders (age, sex, diagnosis, comorbidities, and urbanicity). Simple logistic regression and Pearson correlations will be conducted as preliminary exploratory analyses to inform variable selection for the multivariable model. Pre-post changes in adherence outcomes—including PRE2DUP-derived exposure duration and average daily dose in DDDs, as well as self-report scale scores—will be analyzed using linear mixed-effects models, with time (pre- vs. post-intervention) as a fixed effect and subject as a random effect, adjusting for diagnosis, age, and sex.

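### Patients enter because adherence is poor and are compared only with their own baseline, so the pre-post change cannot be read as effectiveness

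*Protocol article*

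**What the plan says.** Section 2.1 describes the intervention component as "a single-arm pre-post study to evaluate the intervention" and fixes the comparator: "All patients identified with poor adherence will receive the same psychoeducational program; the pre-intervention measurement will serve as a comparator". Section 2.4 fixes entry: "the subset of the sample identified with adherence problems will be the target sample for the intervention".

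Section 2.8 says the investigators will "compare the total duration of antipsychotic exposure in the 6 months prior to the intervention with that in the 6 months following the intervention". The pre-post model in the same section is a linear mixed model with "time (pre- vs. post-intervention) as a fixed effect and subject as a random effect, adjusting for diagnosis, age, and sex".

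Objective 3 (Section 1.5) is to evaluate the effectiveness of the intervention. On numbers, Section 2.3 says: "We therefore set a recruitment target of 110 participants, well within the estimated pool of 656 patients expected to present with poor adherence".

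The limitations (Section 4.3) cover selection through the Patient Portal, dispensing as a proxy for ingestion, attrition, and supply outside the public prescription network. They mention neither regression to the mean nor the lack of a control.

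**The concern.** A patient labelled a poor adherer has a low value partly because of a lasting tendency and partly because of a bad spell. The bad spell tends to pass. If it also lies in the baseline, the next six months look better with no help from the program. Any calendar change in prescribing, dispensing or care over the period is added to this.

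The planned model does not separate these sources. With two complete time points per patient, its time coefficient is the mean within-patient change. Diagnosis, age and sex do not account for selection on a low value. A significant rise could therefore be reported as effectiveness when the program did nothing. This is not a detail left to an analysis plan, because the article itself fixes the comparator, the basis for entry, the contrast and the model.

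**Working it through.** **The plan's own figures (Section 2.3).** With d = 0.5, two-sided alpha 0.05 and power 95%, n = ((1.960 + 1.645)/0.5)² = 51.98, so 52. The exact t calculation gives 54, which is close. Dropout: 52/(1 − 0.5) = 104. Pool: 656/1640 = 40%, within the 40–50% prevalence in Section 2.4. At 50% dropout, 110 recruits leave 55 completers. The sample-size arithmetic is not in dispute.

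**Assumptions.** The article gives neither the correlation ρ between six-month windows nor the cut-off for poor adherence. I assume a normal score with equal mean and SD in each window, the lowest 40% selected, no intervention effect, and ρ from 0.5 to 0.9. For the lowest 40%, the cut-off is c = −0.253, the mean deficit is λ = φ(c)/0.40 = 0.966 SD, and the variance among those selected is v = 1 − cλ − λ² = 0.312.

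**Case A: selection window = baseline window.**
- Expected gain = (1 − ρ)λ.
- Variance of change = (1 − ρ)²v + 1 − ρ².
- Example, ρ = 0.5: gain = 0.5 × 0.966 = 0.483; variance = 0.25 × 0.312 + 0.75 = 0.828; dz = 0.483/√0.828 = 0.53.

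**Case B: windows half overlap.** Each patient has a stable level (variance ρ) plus independent monthly noise, with a three-month shift between the windows.
- The selection value has covariance (1 + ρ)/2 with baseline and ρ with follow-up, so expected gain = λ(1 − ρ)/2.
- Variance of change = 2(1 − ρ) − ((1 − ρ)/2)²(1 − v).
- Example, ρ = 0.5: gain = 0.242; variance = 1 − 0.0625 × 0.688 = 0.957; dz = 0.25.

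Share of simulated null trials with p<0.05 (two-sided paired t-test, 55 completers):

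| ρ | Case A: dz | Case A: p<0.05 | Case B: dz | Case B: p<0.05 |
|---|---|---|---|---|
| 0.5 | 0.53 | about 97% | 0.25 | about 45% |
| 0.7 | 0.39 | about 82% | 0.19 | about 29% |
| 0.8 | 0.32 | about 64% | 0.15 | about 20% |
| 0.9 | 0.22 | about 36% | 0.11 | about 12% |

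The nominal rate is 5% and the planning effect is d = 0.5. In Case A the artefact is 0.22/0.5 = 44% of the planned effect at ρ = 0.9, and exceeds it at ρ = 0.5.

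**Case C: selection window ends before the baseline window starts.** If the correlation is the same between any two windows, the expected artefact is zero. If it decays with time (first-order autoregressive, three consecutive windows), expected gain = ρ(1 − ρ)λ. For ρ = 0.5, 0.7, 0.8 and 0.9 this is 0.24, 0.20, 0.15 and 0.09 SD, or dz 0.25, 0.27, 0.25 and 0.20. The false-positive rate at 55 completers is then about 30% to 50%. Separating the windows reduces the artefact but need not remove it.

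**The case against.** The strongest reply is that the size is not established. Section 2.4 speaks of "we will identify factors associated with adherence issues in the six months prior to the study", and that is for the risk-factor analysis. The baseline in Section 2.8 is the six months before the intervention, and questionnaire invitations come in between, so the windows may overlap only partly. The article also does not say whether dispensing data or a questionnaire identifies poor adherence. The 656 is 40% of the expected questionnaire completers, so either is possible, and selecting on one measure while testing on the other weakens the artefact. Real exposure percentages are bounded and skewed. All of this stands. A reader might infer that the error rate is far above 5% in every case, but the documents do not support that: they state neither identical windows nor the selecting measure.

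A reader might also quote rates for 110 patients (about 63% to 100% in Case A). Section 2.3 expects up to 50% dropout, so 55 is the fair number for the questionnaires. The larger number could apply only to dispensing data, and only if these are kept for dropouts.

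It can also be said that the single arm is a disclosed choice and that the conclusions are cautious, calling for replication. That is true. But Objective 3 still claims effectiveness, and replicating the same design would replicate the bias.

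Finally, the sentence on all identified patients may mean only that there is no second arm. That makes it a wording conflict with the target of 110, not evidence of a different design.

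**Conclusion.** The concern holds, with a conditional size. As written, the effectiveness estimate includes regression to the mean and secular change, the model does not remove them, and the limitations do not mention them. The direction of regression to the mean needs only selection on a low value and imperfect correlation between windows. The size rests on assumptions the article does not supply: about 36% to 97% false positives with identical windows, and about 12% to 45% with half overlap, for correlations of 0.9 down to 0.5. It would be lower again if one measure selects and another is tested. Because the objective is effectiveness, this should be settled before the planned start.

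**What to change.** 1. **Add a concurrent comparison for the dispensing outcome.** Extract the same pre and post MUP windows for eligible poor adherers who are not enrolled (about 656 − 110 = 546), with index dates matched to enrolment. Use the time-by-group difference in change, adjusted for baseline exposure, age, sex and diagnosis, as the effectiveness estimate. Report it as a non-randomised comparison with residual self-selection. First confirm that the Portal consent in Section 2.2 covers these patients, given the Informed Consent Forms in Section 2.7 and the pre-inclusion information in Section 3.7.
2. **Relabel the within-group change.** Call the pre-post change, including the questionnaire scores, descriptive. Add regression to the mean and the absence of a control to Section 4.3.
3. **Optional: separate the windows.** Define poor adherence on a window that ends before the baseline window starts. This reduces the artefact but leaves a dz of about 0.20 to 0.27 if correlation decays with time as in Case C. It also needs patients with enough earlier history.
4. **Reconcile the wording.** Section 2.1 says all identified patients receive the program; Sections 2.3 and 2.4 set a target of 110. If all were treated, the comparison in step 1 would have no patients.

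**Cost.** One more extract from the same database, changes to the protocol and analysis text, and the consent check. Confounding by willingness to take part remains.

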### 2.2. Sample

Our sample consists of patients with a diagnosis of schizophrenia and/or bipolar disorder.

Inclusion criteria:Diagnosis established using ICD-11 clinical criteria (World Health Organization).Aged 18 years or older.Registered on the Patient Portal.With an active prescription for antipsychotic drugs in the MUP.

To participate in the study, patients must have provided informed consent when registering through the Patient Portal, which allows access to their personal data for clinical and scientific purposes.

Exclusion criteria:Aged under 18 years old.Unable to provide consent for medical or legal reasons.Not registered on the Patient Portal.No active prescription for antipsychotic drugs in the MUP.Severe cognitive impairment, as determined by clinical judgment, that prevents the patient from providing informed consent or interacting with digital tools.

### 2.3. Sample Size Calculation

According to our preliminary data, there are 5458 patients in our hospitals diagnosed with schizophrenia or bipolar disorder and with active antipsychotic dispensing registered in the MUP. Of these, an estimated 90% are registered on the Patient Portal, yielding an initial estimated sample of 4900 people.

Considering that completion of self-administered questionnaires on the Patient Portal is estimated to be around 30%, we expect an approximate sample of 1640 patients to perform the validation calculations for the adherence scales.

The sample size was calculated using G*Power (v3.1) for a one-sample means test (alpha = 0.05, power = 95%, effect size d = 0.5), yielding a minimum of 52 participants. This was based on previous studies exploring the ability of educational interventions to improve medication adherence in the medium term (Loots et al., 2021). Accounting for an anticipated dropout rate of up to 50%, the adjusted minimum is 104. We therefore set a recruitment target of 110 participants, well within the estimated pool of 656 patients expected to present with poor adherence.

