Until relatively recently, the main methods available for measuring treatment adherence were self-report questionnaires, which could be administered either on paper or electronically via platforms such as the Patient Portal. This digital communication platform, operational in some hospitals, allows patients to access appointments and reports and to respond to online questionnaires known as PROMs (patient-reported outcome measures), including medication adherence surveys. A major limitation of these self-report tools is their susceptibility to bias: patients with poor adherence may claim they are taking their treatment when they are not, to avoid intervention from healthcare staff. Also, these questionnaires provide only a cross-sectional picture, whereas continuous long-term monitoring would be more accurate and useful. With the advent of digital electronic prescriptions (Roden et al., 2012), a novel approach to assessing adherence has emerged in several countries, including Spain. In the Community of Madrid, the Single Prescription Module (Módulo Único de Prescripción, MUP) provides access to the patient’s pharmacological history and enables prescription management on this platform. Additionally, this prescription system is interoperable with those of other Autonomous Communities across the country. The MUP allows verification that patients have collected their prescribed medications from the pharmacy, providing an objective method to assess treatment adherence. A critical distinction must be made between self-report adherence measures and dispensing-based data. While self-reports are cost-effective and provide insight into the reasons for non-adherence, they are frequently confounded by recall bias and social desirability, leading to an overestimation of compliance (Nguyen et al., 2014). In contrast, new dispensing data processing tools, such as the PRE2DUP-R package (Tanskanen et al., 2015; Vattulainen et al., 2025), provide an objective, longitudinal record of treatment acquisition. Although dispensing data does not guarantee the actual ingestion of the medication, it serves as a more reliable predictor of clinical relapse than subjective scales in severe mental illness and has been validated both in serum concentration and comprehensive drug treatment interview (Forsman et al., 2018; Krousel-Wood et al., 2015; Taipale et al., 2016).

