### 4.3. Limitations

Several limitations of the ADHERA study must be acknowledged. First, there is a potential selection bias inherent in the recruitment through the Patient Portal; participants who are already digitally literate or more engaged with the health system may be overrepresented, potentially limiting generalizability (Misdrahi et al., 2023). Second, our primary outcome relies on pharmacy dispensing data, which serves as a proxy for adherence but cannot confirm medication ingestion. While it remains a good proxy for objective adherence monitoring (Lam & Fresco, 2015), it cannot account for doses that are collected but not consumed. To address this issue, we will use the PRE2DUP-R R package (Tanskanen et al., 2015; Vattulainen et al., 2025). This method provides an objective approach to medication use and has been validated as a measure of medication use relative to both serum concentrations (Forsman et al., 2018) and a comprehensive drug treatment interview (Taipale et al., 2016). Third, telehealth interventions often experience attrition; although our peer-support component aims to mitigate this, some degree of dropout is expected. Finally, while the MUP system provides objective data, it does not capture medication provided through external samples or private clinical settings not integrated into the public electronic prescription network.

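### PPV and NPV will come only from the roughly 30% of portal patients who return a questionnaire, although MUP adherence is held for everyone invited; whole-sample values should be reported beside them

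*Protocol article*

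**What the plan says.** Section 2.3 of the protocol article starts from a count: "there are 5458 patients in our hospitals diagnosed with schizophrenia or bipolar disorder and with active antipsychotic dispensing registered in the MUP". Taking nine in ten of them to be portal users, it arrives at about 4900 people to invite. It then says that "completion of self-administered questionnaires on the Patient Portal is estimated to be around 30" per cent, and concludes from this: "we expect an approximate sample of 1640 patients to perform the validation calculations for the adherence scales". The validation sample is therefore the group of completers.

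Section 2.4 says who is asked: "The entire sample will then be invited via a message through the Patient Portal to complete the self-report adherence questionnaires". The same section has adherence problems over the preceding six months examined in the whole sample before that invitation goes out. Section 2.2 makes an active antipsychotic prescription in the MUP an inclusion criterion. The reference standard therefore exists for people who never answer.

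Section 2.8 names the output: "sensitivity, specificity, positive predictive value, and negative predictive value will be calculated using medication collection data from the MUP as the gold standard". It does not say to which population the predictive values refer.

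Section 4.3 concedes, about recruitment through the portal, that "participants who are already digitally literate or more engaged with the health system may be overrepresented". The article describes no adjustment for this.

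**The concern.** Sensitivity and specificity are calculated within poor adherers and within adherers, so a change in the mix of the two groups alone does not move them. PPV and NPV do move with that mix. If the people who answer a portal message have a different rate of poor adherence from the people who were invited, responder PPV and NPV describe the responders and nobody else.

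Non-response is by far the larger filter. Portal registration removes about 10% of the MUP population; non-completion removes about 70% of what is left.

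Objective 1 (section 1.5) is to validate the digital questionnaires against dispensing data. A reader who takes an unqualified NPV as applying to all portal patients could place too much or too little trust in the questionnaire, depending on which way response differs. Usually the rate in the target population has to be guessed. Here it will be measured, because MUP exposure is extracted for the whole sample.

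**Working it through.** **The plan's own figures.**
- Portal sample: 0.90 × 5458 = 4912, stated as 4900. This reproduces.
- Completers: 0.30 × 4900 = 1470, not 1640. The stated 1640 matches 0.30 × 5458 = 1637, so the 30% seems to have been applied before the portal step; 1640 would be 33.5% of 4900. This should be tidied but does not affect the point.
- Invited patients with MUP data but no questionnaire: 4900 − 1470 = 3430, or 4900 − 1640 = 3260.

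**Inputs for the illustration.**
- Poor adherence in the whole sample, p: 40% and 50%, the two ends of the range in section 2.4.
- Response ratio r (response among poor adherers divided by response among adherers): 1, 0.75, 0.5 and 1.5. Assumed; the article gives none.
- Sensitivity (Se) and specificity (Sp): both 0.70, with a positive result meaning poor adherence. Assumed, and taken to be the same in responders and non-responders.

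**Formulas.**
- Prevalence among responders: q = p·r / (p·r + 1 − p)
- PPV = Se·q / [Se·q + (1 − Sp)(1 − q)]
- NPV = Sp·(1 − q) / [Sp·(1 − q) + (1 − Se)·q]

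**Worked case, p = 0.40, r = 0.5.**
- q = 0.20 / (0.20 + 0.60) = 0.25
- Responders: PPV = 0.175 / (0.175 + 0.225) = 0.44; NPV = 0.525 / (0.525 + 0.075) = 0.88
- Whole sample (use p in place of q): PPV = 0.28 / (0.28 + 0.18) = 0.61; NPV = 0.42 / (0.42 + 0.12) = 0.78

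| p | r | q | PPV, responders (whole sample) | NPV, responders (whole sample) |
|---|---|---|---|---|
| 0.40 | 1 | 0.40 | 0.61 (0.61) | 0.78 (0.78) |
| 0.40 | 0.75 | 0.33 | 0.54 (0.61) | 0.82 (0.78) |
| 0.40 | 0.5 | 0.25 | 0.44 (0.61) | 0.88 (0.78) |
| 0.40 | 1.5 | 0.50 | 0.70 (0.61) | 0.70 (0.78) |
| 0.50 | 0.5 | 0.33 | 0.54 (0.70) | 0.82 (0.70) |

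The last row with p = 0.40 shows the reversal: q = 0.60 / (0.60 + 0.60) = 0.50.

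**Other accuracy values.** Over Se/Sp of 0.5/0.8, 0.7/0.7 and 0.4/0.9, with p of 40% or 50%, r = 0.5 moves PPV by −0.13 to −0.17 and NPV by +0.10 to +0.15.

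**Against sampling error.** In the worked case 1470 responders give 1470 × 0.40 = 588 positive and 882 negative results. The 95% half-widths are 1.96 × √(0.4375 × 0.5625 / 588) = 0.04 for PPV and 1.96 × √(0.875 × 0.125 / 882) = 0.02 for NPV. The shifts of 0.17 and 0.10 are about four times as large, so the confidence interval would not reveal them.

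**Does the correction work?** In a simulation with p = 0.40, Se 0.5, Sp 0.8, r = 0.5 and response depending on MUP adherence only, responder values were PPV 0.456 and NPV 0.827. Weighting by the inverse of the response probability gave 0.626 and 0.706, against whole-sample values of 0.625 and 0.705.

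**Precision cost of weighting on adherence alone** (Kish effective fraction, p = 0.40).
- r = 0.5: a quarter of responders have relative weight 2, the rest 1. (0.25 × 2 + 0.75)² / (0.25 × 4 + 0.75) = 1.5625 / 1.75 = 0.893, a loss of 11%.
- r = 0.75: a third have relative weight 4/3. (10/9)² / (34/27) = 0.98, a loss of 2%.

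**The case against.** **The analysis plan is not shown.** It may contain a comparison of responders with non-responders, and a condensed article need not. This stands: the missing non-response analysis is not itself the fault. What remains is that the article fixes completers as the validation sample and promises PPV and NPV without saying whom they describe.

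**Responders may be the right population.** In routine use a predictive value is applied to a returned questionnaire, so the people who return one are a legitimate target. This also stands. A reader might infer that weighted estimates should replace the responder values as the main result. The article does not support that; the two answer different questions, and the whole-sample values belong beside the responder values.

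**Lower response among poor adherers is not documented.** A reader might infer it from section 1.2, which says that "patients with poor adherence may claim they are taking their treatment when they are not, to avoid intervention from healthcare staff". That sentence describes answering falsely, not declining to answer; a patient with that motive could well respond. Section 4.3, on engaged patients being overrepresented, is closer support but gives no direction or size for response by adherence.

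**The 40% figure.** A reader might take the 656 poor adherers in section 2.3 as the whole-sample rate. Since 656 = 0.40 × 1640, it is a ratio based on the expected responders. The illustration therefore takes its 40% from the range in section 2.4.

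**The issue is partly acknowledged.** Section 4.3 names selection through the portal, and the invitation itself goes through the portal, so it would be too narrow to read it as covering registration only. But it is offered as a limit on generalizability, with no correction planned from the MUP data already held.

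**Conclusion.** The point holds as an inexpensive improvement to the validation analysis. As planned, PPV and NPV apply to the roughly 30% who return a questionnaire, while the data needed to speak for the whole portal sample will already be in hand.

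The size and direction of any shift cannot be derived from the article. A halved response among poor adherers would move PPV by about −0.17 and NPV by about +0.10 under the assumed 40% prevalence and accuracy of 0.70. If response is unrelated to adherence and to accuracy, nothing moves. A reader might infer that the questionnaires will look better at ruling out poor adherence than they are; that follows only if poor adherers respond less, which the article does not establish.

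Sensitivity, specificity and the Youden cut-off do not change with prevalence alone. They would change if responders differ from non-responders in how accurately they report. Reweighting on measured variables corrects that only as far as those variables explain the difference.

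**What to change.** In section 2.8:

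1. Compare MUP exposure and baseline covariates (age, sex, diagnosis, urbanicity, comorbidities) between responders and non-responders in the whole invited sample.
2. Keep the responder sensitivity, specificity, PPV and NPV, and state that the predictive values apply to returned questionnaires.
3. As a prespecified accompanying analysis, report either PPV and NPV recalculated at the whole-sample MUP prevalence, or all four measures weighted by the inverse probability of response, with bootstrap intervals.
4. State the assumption: accuracy carries over to non-responders given the measured variables. The recalculation at whole-sample prevalence makes the stronger form of it, since it uses the responder sensitivity and specificity unchanged.

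The cost is a few sentences and a little more analysis, with no new data collection. Weighted intervals will be somewhat wider. The 2–11% loss of effective sample size shown above covers weighting on adherence alone and would usually be larger with more covariates in the response model. While editing section 2.3, reconcile 1640 with 30% of 4900.
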